#### Data analysis

2.2.7

Data analysis will include descriptive statistics and exploratory analysis to determine the normality of the distributions and to check the range of data values. Bivariant analysis will be performed by chi‐square test, Student *t* test, Mann–Whitney U, Wilcoxon W, ANOVA, and Kruskal–Wallis test, depending on the normality of the distributions, type of variable analysed, and their homoscedasticity, which will be tested by the Levene's test. Intra‐group analysis will be performed by general linear models, with the corresponding corrections in multiple comparisons by Bonferroni test. To test the null hypothesis (inter‐group analysis), lineal generalized models will be developed in repeated measures, taking on consideration CFUs number as dependent variable as well as control or experimental designation group as a factor. Even if basal differences are significative, they will be attached as adjustment factor, following Mallinckrodt and Lipkovich recommendations (Mallinckrodt, Lipkovich, & Lipkovich, 2016). Sphericity will be tested using Mauchly test, Greenhouse‐Geisser test, or Huynh‐Feldt test in case of no setting.

All analyses will be performed by an intention‐to‐treat approach. To this purpose, missing data will be calculated by multiple imputation methods.

All the analyses will be performed in a blinded way.

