**Methods:**

Patients with chronic venous leg ulcers with signs of critical colonization will be randomized in a concealed sequence using computer software to receive one of the alternative dressings. A total of 204 participants recruited in Primary Health Care and nursing homes will be necessary to assure statistical power. Measures will include sociodemographic variables, wound‐related variables (area, exudate, and time to healing), level of pain, adverse effects, and health‐related quality of life. Smear samples will be collected from the ulcers and will be subject to DNA‐typing technique through polymerase chain reaction to obtain the level of colony‐forming units. Measures will be collected at baseline, 4, 8, and 12 weeks.

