#### Data collection

2.2.5

Patients will be recruited by clinical nurses in health centres and nursing homes belonging to the District of Primary Health Care of Málaga (Spain). Following obtaining the patients’ informed consent, sociodemographic variables (age, gender), wound location and characteristics, and current treatment will be collected at baseline, together with the endpoints by the nurse who usually give care to the patient. This will reinforce the patient adherence to the study.

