##### Secondary outcome measures

Wound size will be evaluated by planimetry using PictZar^®^ 7.6.1 software (Wendelken et al., 2011). Photos will be taken from affected area completely in parallel with respect to the ulcer and the photo will have to include a calibrated rule of 3 cm (standardized procedure according to PictZar^®^ planimetry). The characteristics and clinical evolution of the wound will be evaluated using the Resvech 2.0 scale (Restrepo‐Medrano & Verdú Soriano, 2011).

Healing time will be measured by the number of days until complete healing. This outcome will be complied if re‐epithelialization of the skin is confirmed in two consecutive visits across 2 weeks. Pain will be measured using the Numerical Rating Scale (NRS).

Health‐related quality of life will be measured by means of the Charing Cross Venous Ulcer Questionnaire (CCVUQ) (González de la Torre, Quintana‐Lorenzo, Perdomo‐Pérez, & Verdú, 2017; González‐Consuegra & Verdú, 2010). Adverse events related to the treatment will be collected both by nurses and patients. Follow‐up will be carried out at 4, 8, and 12 weeks, except the quality of life, which will be only evaluated at baseline and 12 weeks. Adherence to the treatment will be checked with the nurse and with the evaluation of consumed dressings.

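### Pain, CCVUQ and Resvech 2.0 would, on the natural reading, be compared by unadjusted tests chosen from the trial data, although their baseline values are collected

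*Protocol article*

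**What the plan says.** All references are to the protocol article.

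- **Test choice.** Data analysis (2.2.7) begins with "exploratory analysis to determine the normality of the distributions". It then lists chi-square, t, Mann–Whitney, Wilcoxon, ANOVA and Kruskal–Wallis tests, to be chosen "depending on the normality of the distributions, type of variable analysed, and their homoscedasticity", with Levene's test for the variances.
- **Between-arm model.** The general linear models in that section are for comparisons within a group. The one model labelled as inter-group is a repeated-measures model, "taking on consideration CFUs number as dependent variable as well as control or experimental designation group as a factor".
- **Baseline adjustment.** The next sentence reads "Even if basal differences are significative, they will be attached as adjustment factor". No secondary outcome is named there.
- **Baseline data.** Under Data collection (2.2.5), patient and wound characteristics "will be collected at baseline, together with the endpoints by the nurse". The abstract says "Measures will be collected at baseline, 4, 8, and 12 weeks", and Secondary outcome measures makes an exception for quality of life, "which will be only evaluated at baseline and 12 weeks". Pain (NRS), CCVUQ and Resvech 2.0 therefore all have a baseline value.

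**The concern.** A t-test concerns a difference in means and a Mann–Whitney test a difference in ranks. If observed normality and Levene's test decide between them, the quantity reported for an outcome is known only after the data have been seen, and it may differ between outcomes or visits. Neither test uses the patient's own starting value. Where baseline and follow-up are correlated, leaving it out gives wider intervals and lower power than the collected data allow. At stake is how precise and how comparable the results on pain, quality of life and the wound scale will be.

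**Working it through.** **1. The plan's own figure.** Sample (2.2.2) gives 93 per arm for 80% power at 95% confidence. Two-sided 5% is assumed here, because sidedness is not stated. No SD or base rate is given, so the figure can be matched only by assumption. For a comparison of means it corresponds to a standardized difference of

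d = (1.960 + 0.842) × √(2/93) = 2.802 × 0.1466 = 0.411.

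(50% against 30% also gives 93 per arm.) That calculation is for bacterial load, and the plan claims no power for any secondary outcome. The value d = 0.411 serves below only as a reference: a comparison with 80% power when unadjusted.

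**2. Effect of adjustment.** With baseline–follow-up correlation ρ, adjustment multiplies the SD by √(1 − ρ²). Power is then Φ(2.802/√(1 − ρ²) − 1.960), and the number per arm for 80% power is 93 × (1 − ρ²), rounded up. The documents give no ρ, so a range is shown.

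| ρ (assumed) | √(1 − ρ²) | SE smaller by | Power at 93 per arm | n per arm for 80% |
|---|---|---|---|---|
| 0 | 1 | 0% | 80.0% | 93 |
| 0.3 | 0.954 | 4.6% | Φ(0.98) = 83.6% | 85 |
| 0.5 | 0.866 | 13.4% | Φ(1.28) = 89.9% | 70 |
| 0.7 | 0.714 | 28.6% | Φ(1.96) = 97.5% | 48 |

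**3. Behaviour of the selection rule.** This was simulated with 93 per arm, 2,000 trials per setting and ρ = 0.5. The plan names no normality test, so Shapiro–Wilk at 5% in each arm was assumed. Mann–Whitney was used if that test or Levene's test rejected, and the t-test otherwise. The comparator was an untransformed linear model with treatment and baseline. The pain-like score was rounded and limited to 0–10, with assumed means of 6 at baseline and 4 at follow-up and an SD of 2.2.

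| Outcome shape | Mann–Whitney chosen | Type I error, rule | Power, rule | Power, adjusted |
|---|---|---|---|---|
| Normal | 14–15% | 4.6% | 77.7% | 89.1% |
| Mild skew (gamma, shape 8) | 90–91% | 4.5% | 81.6% | 89.6% |
| Strong skew (gamma, shape 3) | 100% | 4.8% | 87.6% | 88.3% |
| Pain-like 0–10 score | over 99% | 5.4% | 78.5% | 86.9% |

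The test chosen depends heavily on the shape of the data, while the type I error stays near 5%. At ρ = 0.5 adjustment adds about 8 to 11 points of power, except under strong skew, where the rank test recovers nearly all of it (a difference of 0.7 points).

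**The case against.** The strongest objection is that the article never expressly assigns the bivariate tests to the secondary outcomes. The sentence is a general list, it includes tests that a two-arm comparison does not need, and the baseline-adjustment sentence could be read as covering every outcome. The article is also condensed, and outcome-by-outcome models are commonly left to a full protocol or SAP. This stands in part: the reading is an inference, and a reader should not conclude that the plan rules out adjustment for secondary outcomes. But the selection rule is stated in the article, so it is not a detail merely left out, and no other between-arm method is named for these outcomes. A plan that intends adjustment throughout still needs this sentence changed.

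Further limits stand:

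- Normality is to be judged by exploratory analysis, with no formal test named. The Shapiro–Wilk rule is an assumption of the check.
- The choice also depends on variable type, which could settle a rank test for pain in advance. In the simulation the pain-like score went to Mann–Whitney almost every time, so for pain the visible cost is precision more than a changing test.
- The gain depends on ρ and is modest at 0.3. Severe pain at dressing change is one of the five entry signs, of which three are required. That may narrow baseline pain and lower ρ.

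A reader might infer that choosing tests by pre-testing inflates false positives, or that the primary result is at risk. Neither is supported: the simulated error rate was 4.5–5.4%, and CFUs have their own model.

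**Conclusion.** The point holds as an improvement at no cost in data, not as an error that invalidates an analysis. On the natural reading of Data analysis, pain, CCVUQ and Resvech 2.0 would be compared without their baseline values and with an effect measure not fixed in advance. For a comparison with 80% unadjusted power at 93 per arm, adjustment would give about 84%, 90% or 98% at an assumed ρ of 0.3, 0.5 or 0.7, with standard errors about 5%, 13% or 29% smaller. Under strong skew there is little gain.

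It would go too far to say that the secondary comparisons as a whole lose precision. Total healing, healing time and adverse events have no baseline value of the outcome and fall outside this point. The proportion of wound reduction already uses baseline area.

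**What to change.** For pain, CCVUQ and Resvech 2.0, replace the test-selection sentence with one pre-stated model: a linear model, or a repeated-measures model for outcomes measured at 4, 8 and 12 weeks, with treatment and the baseline value of the same outcome, and robust standard errors. Report the adjusted mean difference and its 95% interval whatever the normality or Levene result, and keep the rank test as a sensitivity analysis. If the existing adjustment sentence was meant to cover these outcomes, say so.

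If wound area itself is analysed, adjust for baseline area on a scale that admits zero. A log scale does not serve, because a healed ulcer has area zero.

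The cost is protocol or SAP wording only. The baseline values are already collected, and no visits or participants are added.

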### Aim

2.1

The main aim of the study is to determine the effectiveness of a hydrophobic dressing (Cutimed Sorbact^®^) against a silver dressing (Aquacel^®^ Ag Extra) in the level of colonization of chronic venous leg ulcers.

The secondary aims will be to analyse the effect of Cutimed Sorbact^®^ versus Aquacel^®^ Ag Extra on total healing, the proportion of wound reduction, time of recovery, level of pain during recovery, and health‐related quality of life. In addition, the safety of Cutimed Sorbact^®^ will be evaluated.

The null hypothesis is that there is no difference in the level of bacterial colonization at 12 weeks of follow‐up in chronic ulcers treated with Cutimed Sorbact^®^ versus those treated with Aquacel^®^ Ag Extra.

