#### Sample

2.2.2

Assuming a 95% confidence level and 80% statistical power, 186 participants would be necessary (93 for each study arm) to detect a 20% load bacteria reduction (Mosti et al., 2015). This sample will be increased up to 204 participants to cover any possible patient dropouts.

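### The primary repeated-measures model names CFU number and a group factor, but neither a log scale nor the week-12 contrast that the null hypothesis concerns

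*Protocol article*

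**What the plan says.** The null hypothesis in Aim (2.1) is that "there is no difference in the level of bacterial colonization at 12 weeks" of follow-up between the two dressings. Measures are taken at baseline and at weeks 4, 8 and 12 (Abstract, Methods).

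For the test of that hypothesis, Data analysis (2.2.7) states that "lineal generalized models will be developed in repeated measures, taking on consideration CFUs number as dependent variable", with the assigned group as a factor. It adds: "Sphericity will be tested using Mauchly test", with Greenhouse-Geisser or Huynh-Feldt as the alternatives. Baseline differences are to enter as an adjustment factor, in a sentence that ties this to whether they are significant. Normality is explored, but the choice of method by normality is stated only for the bivariate tests. Missing data are multiply imputed.

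Primary endpoint (2.2.5) standardises results to CFU per microlitre and names no log scale. The infection threshold in the inclusion criteria is a power of ten (10^5). Sample (2.2.2) states that "186 participants would be necessary (93 for each study arm) to detect a 20% load bacteria reduction", with no SD, control value or scale.

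**The concern.** Two features of the stated test fit the question poorly.

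- **Scale.** Mauchly's test and the Greenhouse-Geisser and Huynh-Feldt corrections belong to normal-theory repeated-measures ANOVA. The response named for that model is the CFU number. Bacterial load read off a serial-dilution curve and judged against 10^5 can be expected to vary multiplicatively. On the raw scale a few very high counts then drive both the arm mean and its variance.
- **Target.** A group factor in a repeated-measures model compares the arms averaged over the modelled visits. The hypothesis is about one visit, week 12. If baseline is among the modelled visits, the average also includes a time at which no treatment effect can exist.

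This is the only test named for the primary hypothesis. With scale, visit and role of baseline all unsettled, several different primary p-values could be produced from the same data, and some of these tests are clearly weaker than others.

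**Working it through.** **Inputs from the article.** 93 per arm, 1:1; 80% power; 95% confidence (taken as two-sided 5%); visits at baseline and weeks 4, 8 and 12.

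**Assumed, because the article does not give them.** Log-normal CFU; SD on log10 of 0.3 to 1.5; equal correlation rho between visits (0.5, range 0.3 to 0.7); an effect that builds linearly to week 12, or alternatively appears in full by week 4.

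**The article's own figure.** 186 cannot be reproduced from the stated inputs. For a comparison of means, 93 per arm implies d = (1.960 + 0.842) × sqrt(2/93) = 0.411 SD (0.413 with the t distribution). A comparison of 50% with 30%, or of 70% with 50%, also gives 93 per arm, but those rates are not in the article. The benchmark below is therefore a shift of 0.413 SD on log10, which has 80% power for an unadjusted week-12 test at 93 per arm.

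**Step 1: scale.** Simulated week-12 t test on 10^x against the same test on x:

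| log10 SD (assumed) | Power on log10 | Power on raw CFU |
|---|---|---|
| 0.3 | 80% | about 71% |
| 0.5 | 80% | about 55% |
| 1.0 | 80% | about 22% |
| 1.5 | 80% | about 8% |

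Repeat runs differ by a point or so. The loss is about 9 points at SD 0.3, 25 at SD 0.5 and 58 at SD 1.0.

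**Step 2: target, baseline as one of four averaged visits (log10 scale, linear build-up).**
- Effect carried by the group term: mean of (0, 1/3, 2/3, 1) = 0.5 of the week-12 effect.
- Variance of a four-visit mean: (1 + 3 × 0.5)/4 = 0.625; SD 0.791.
- d = 0.413 × 0.5/0.791 = 0.261; power about 43% (53% at rho 0.3, 36% at rho 0.7).
- If the full effect is present by week 4, simulated power is about 76%.

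**Step 3: target, baseline as covariate and weeks 4, 8 and 12 averaged (log10 scale, linear build-up, rho 0.5).**
- Effect carried: mean of (1/3, 2/3, 1) = 2/3.
- Residual variance: (1 + 2 × 0.5)/3 − 0.5² = 0.417; SD 0.645.
- d = 0.413 × (2/3)/0.645 = 0.427; power about 82%.
- Week-12 contrast with the same adjustment: d = 0.413/sqrt(1 − 0.5²) = 0.477; power about 90%.
- At rho 0.3 the pair is 80% and 84%; at rho 0.7 it is 92% and 98%.

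**Step 4: both features together.** In simulation with rho 0.5 and linear build-up, the four-visit group term on raw CFU has 35%, 27% and 10% power at SD 0.3, 0.5 and 1.0.

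**Step 5: what the log scale cannot do.** If the 20% in Sample is a relative reduction in CFU, it equals −log10(0.8) = 0.097 log10. With 93 per arm, 80% power then requires a log10 SD of about 0.097/0.411 = 0.236. At SD 0.5 the log-scale power is 26% (418 per arm needed), and at SD 1.0 it is 10% (1672 per arm needed).

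**The case against.** The strongest reply is that a journal article condenses a fuller document, and that transformation, covariance and contrasts are commonly fixed there. The article never says that counts stay untransformed, and its model wording could mean a generalized linear model, where a raw count with a log link is proper. Sphericity concerns within-subject effects, so citing it points towards a group-by-time test rather than the group main effect. The article mentions baseline adjustment, and under that reading the loss from averaging is 3 to 8 points rather than 37. Corrected repeated-measures ANOVA after multiple imputation is also a legitimate method.

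Much of this stands, and it rules out three stronger readings that a reader might infer:

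- *The counts are certainly analysed untransformed.* This is the plain reading, but it is not stated.
- *Most of the power is lost.* That holds only at an assumed log10 SD of about 1 or more. At 0.3 to 0.5 the loss from scale is about 9 to 25 points.
- *The week-12 null is not tested.* A repeated-measures model can supply that contrast; the article does not name it.

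The reply does not remove the point. The article goes beyond silence: it commits the primary test to a named response, a treatment term and checks that belong to normal-theory ANOVA. Those checks make a log-link count model an awkward reading. An omnibus group-by-time test is not the week-12 difference either. On raw CFU its simulated power was 46–60%, 23–31% and 3–5% at SD 0.3, 0.5 and 1.0, against 68–84% on log10.

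**Conclusion.** The point holds in limited form. The stated primary model does not match the week-12 hypothesis, and as written it is a poorer test for an outcome likely to vary multiplicatively. The article fixes neither the CFU scale nor the week-12 group contrast, and leaves the role of baseline ambiguous.

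The cost ranges from modest to severe. From scale alone, power falls from 80% to about 71%, 55% or 22% at log10 SD 0.3, 0.5 or 1.0. From averaging alone, with linear build-up and rho 0.5, it is 43% if baseline is averaged in, or about 82% against 90% if baseline is a covariate. Every figure rests on assumed log-normality, SDs, correlation and effect pattern, none of which the article gives. The direction of the scale effect needs only strong right skew. That the visit average differs from the week-12 difference needs only an effect that changes over time or a baseline included in the average.

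**What to change.** In Data analysis (2.2.7), or in the SAP if one exists, state that:

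- the response is log10 bacterial load;
- baseline log10 load is always a covariate, whether or not the arms differ at baseline;
- the model covers weeks 4, 8 and 12 with group, visit and group-by-visit;
- the week-12 group contrast, back-transformed to a geometric mean ratio with 95% CI, is the primary test.

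If a mixed model with unstructured covariance is used, the sphericity steps become unnecessary. That follows from the choice of model; the steps are not an error in themselves.

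The cost is a few sentences and no new data. The downside is that values below the detection limit need a stated rule, such as a fixed substitution with a censored-data sensitivity analysis. The sample-size statement should separately say on what scale the 20% reduction is defined and with what SD, because the change of model does not by itself secure 80% power for it.

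### Baseline adjustment in the primary model appears to depend on significant baseline differences, and no baseline covariate is fixed in advance

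*Protocol article*

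**What the plan says.** Section 2.2.7 (Data analysis) sets the between-group test of the null hypothesis: "lineal generalized models will be developed in repeated measures, taking on consideration CFUs number as dependent variable", with "control or experimental designation group as a factor". Group is the only model term named. The sentence that follows is the only one on baseline: "Even if basal differences are significative, they will be attached as adjustment factor". It cites a methods reference but names no variable and does not say what happens when baseline differences are not significant.

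Baseline values will exist. The Abstract states "Measures will be collected at baseline, 4, 8, and 12 weeks", and section 2.2.5 (Data collection) has the endpoints recorded at baseline. The article does not say whether baseline load is a level of the repeated outcome or stands outside it. The null hypothesis in section 2.1 (Aim) concerns colonisation at 12 weeks.

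Section 2.2.2 (Sample) plans 93 per arm, "Assuming a 95% confidence level and 80% statistical power", "to detect a 20% load bacteria reduction". It gives no SD, base rate or scale.

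**The concern.** Allocation is random (section 2.2.3), so any baseline difference between the arms is due to chance. Its p-value says nothing about whether a covariate is worth including. What decides that is how well the baseline variable predicts the outcome. Baseline bacterial load is the obvious candidate for the primary outcome, and it is already measured.

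If covariates enter because they differ significantly, three things follow. The adjusted model is used in few trials, so most of the available precision is not taken up. A moderate chance imbalance that just misses significance is left in the treatment estimate. And which primary model is fitted is settled only after the baseline data have been tested.

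**Working it through.** **Inputs**

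- Significance level 0.05 and power 0.80 (section 2.2.2). Sidedness is not stated; two-sided is assumed, because the null hypothesis is no difference.
- 93 per arm before dropouts (section 2.2.2).
- Effect in SD units: not given, back-solved in step 1.
- Correlation ρ between baseline and follow-up load: not given, assumed from 0 to 0.7.
- Simplification: one normally distributed follow-up value with equal variances, not the full repeated-measures model.

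**Step 1: the plan's own figure.** The 93 per arm can be neither confirmed nor refuted, because the 20% reduction comes without an SD or base rate. Comparing two proportions (pooled variance, no continuity correction) gives exactly 93 for 50% against 30%, but those rates are an assumption. Comparing two means gives 93 when the standardised difference is

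d = (1.960 + 0.842) × √(2/93) = 2.802 × 0.1466 = 0.411.

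The second route is used below because section 2.2.7 models a count of colony-forming units.

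**Step 2: how often the trigger fires.** Under randomisation, a 5% test of one baseline variable is significant in about 5% of trials (simulated: 4.8% to 5.0%). About 95% would be analysed without that covariate.

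**Step 3: power.** Baseline adjustment multiplies the residual variance by 1 − ρ², so power = Φ(2.802/√(1 − ρ²) − 1.960). At ρ = 0.5 this is Φ(2.802/0.866 − 1.960) = Φ(1.275) = 89.9%. The n per arm for 80% power is 93 × (1 − ρ²), rounded up. The conditional rule was simulated with 40,000 trials per setting, adjusting only if the baseline t test has p < 0.05.

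| ρ | Always adjust (formula) | n per arm for 80% | Always adjust (simulated) | Adjust only if significant (simulated) | Loss, points | Type I error, conditional rule |
|---|---|---|---|---|---|---|
| 0 | 80.0% | 93 | 79.4% | 79.5% | about 0 | 0.050 |
| 0.3 | 83.6% | 85 | 83.0% | 80.2% | 2.8 | 0.046 |
| 0.5 | 89.9% | 70 | 89.6% | 80.7% | 8.9 | 0.044 |
| 0.7 | 97.5% | 48 | 97.1% | 81.2% | 16.0 | 0.036 |

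The loss is the difference of the two simulated columns before rounding (at 0.7: 97.14 − 81.17 = 15.97).

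**Step 4: imbalance left in.** The largest non-significant baseline difference is 1.960 × 0.1466 = 0.287 SD. Unadjusted, it shifts the estimate by ρ × 0.287:

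- ρ = 0.3: 0.086 SD, or 21% of 0.411
- ρ = 0.5: 0.144 SD, or 35%
- ρ = 0.7: 0.201 SD, or 49%

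These are worst cases, with the imbalance exactly at the threshold.

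**Step 5: if baseline is a level of the repeated outcome.** A change-from-baseline contrast has variance factor 2(1 − ρ), so power = Φ(2.802/√(2(1 − ρ)) − 1.960). That gives 65.8%, 80.0% and 95.1% at ρ = 0.3, 0.5 and 0.7, against 83.6%, 89.9% and 97.5% with baseline as a covariate. Since 2(1 − ρ) − (1 − ρ²) = (1 − ρ)², which is never negative, the change contrast cannot beat adjustment at any ρ. The same 0.287 SD imbalance would then shift the estimate by −(1 − ρ) × 0.287, which is −0.144 SD at ρ = 0.5, the opposite direction from step 4.

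**The case against.** The strongest reply is that the sentence does not state the rule being criticised. It does not contain the word *only*, and *even if* could be read as adjustment whatever the test shows. It speaks of baseline differences in general, so it may be aimed at the recorded confounders in section 2.2.9 (antibiotic or analgesic therapy, nutritional status, dependence) rather than at bacterial load. This stands. A reader might infer that the plan adjusts for baseline colonisation only when the arms differ significantly, but the article does not say so. What remains is that no sentence makes baseline load a standing covariate, and the one sentence on baseline brings in significance.

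The second reply is that the model is a repeated-measures one, and baseline may already be a level of it. That is possible, and the loss would then differ from the table. It does not rescue the rule, because step 5 shows that such a contrast does no better than baseline adjustment.

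The third reply concerns harm. A reader might infer a biased estimate or a raised false-positive rate. Neither follows. Over all randomisations the unadjusted estimate is unbiased, the shift in step 4 is conditional on the imbalance seen, and the simulated type I error is 0.036 to 0.050. Nor is the trial underpowered on this account: the sample size claims no gain from baseline adjustment, so what is lost is extra efficiency. A fixed rule applied by blinded analysts is also not a free choice of model after the fact. All of this is accepted.

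Full covariate lists are commonly left to an analysis plan, which is not shown. The point here is narrower: the rule that the article does print is a poor one or an unclear one.

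**Conclusion.** The point holds in a limited form. Section 2.2.7 appears to tie baseline adjustment to significant baseline differences and fixes no baseline covariate. Significance is the wrong criterion in a randomised trial. If it is the operative rule and covers baseline load, the cost against always adjusting is about 3, 9 or 16 points of power at correlations of 0.3, 0.5 or 0.7, and nothing at zero. A chance imbalance just below significance would also go uncorrected.

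The size rests on assumed correlations, on an effect of 0.41 SD back-solved from the sample size, and on a single follow-up value. It would not carry over as it stands if the sample size was built on proportions. This is a matter of efficiency and of fixing the model in advance, not of validity. The change should be made, because always adjusting costs essentially nothing even when baseline does not predict outcome.

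**What to change.** Replace the sentence on baseline differences in section 2.2.7 with:

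*Baseline bacterial load (on the scale used for the outcome) is included as a covariate in the primary repeated-measures model of post-baseline values, regardless of observed baseline differences; significance tests of baseline differences will not be used to choose covariates.*

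This settles both ambiguities, namely whether adjustment is conditional and whether baseline is a covariate or a level of the outcome. The cost is one sentence here, matched in the analysis plan if there is one, and advance notice to the ethics committee, which section 2.2.8 already requires for changes to the analyses. No new data are needed and the sample size does not change.
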